**Methods and analysis:**

This cross-sectional study will recruit 288 participants (91 ME/CFS, 61 individuals with chronic fatigue, 91 healthy controls with sedentary lifestyles, 45 fibromyalgia). The ME/CFS will be diagnosed by consensus diagnosis made by two clinicians using the Canadian Consensus Criteria 2003. Symptoms, vital signs, and activity measures will be collected alongside multimodal MRI.

The HRF, RRF, and glutamate changes will be compared among four groups using one-way analysis of covariance (ANCOVA). Equivalent non-parametric methods will be used for measures that do not exhibit a normal distribution. The activity measure, body mass index, sex, age, depression, and anxiety will be included as covariates for all statistical analyses with the false discovery rate used to correct for multiple comparisons.

The data will be randomly divided into a training (*N* = 188) and a validation (*N* = 100) group. Each MRI measure will be entered as input for a least absolute shrinkage and selection operator—regularized principal components regression to generate a brain pattern of distributed clusters that predict disease severity. The identified brain pattern will be integrated using multimodal deep Boltzmann machines as a neuromarker for predicting ME/CFS fatigue conditions. The receiver operating characteristic curve of the identified neuromarker will be determined using data from the validation group.

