## Introduction

Myalgic encephalomyelitis/chronic fatigue syndrome (ME/CFS) is a serious, long-term illness for which the underlying disease process remains unknown, and no objective diagnostic test exists. The disease is characterized by profound fatigue for more than 6 months, cognitive and motor dysfunction, unrefreshing sleep, and/or orthostatic intolerance (1). There are 17 to 24 million people affected by ME/CFS, with 25% of them housebound (2). In addition to enduring the disease itself and its economic burden, 80% of ME/CFS patients struggle to get a diagnosis and are often left depressed by the lack of a diagnostic certainty and medical understanding of the disease processes. Although the etiology of ME/CFS remains unresolved, the well-documented autonomic dysfunction, sleep disturbance, cognitive impairments, altered sensory and pain perception, and reduced motor speed suggest that abnormal brain function plays a crucial role in the underlying disease process of ME/CFS (3). As such, ME/CFS has been classified as a neurological disease (ICD code 10 G93.3) by the WHO.

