### The recruitment and selection of the sample population

We will recruit 288 adult participants (18–65 years old), including 91 patients with ME/CFS, 61 individuals with chronic fatigue, 91 HCs with sedentary lifestyles, and 45 patients with fibromyalgia. The risk of an ill-defined ME/CFS patient cohort will be mitigated by employing a consensus diagnosis of ME/CFS from two clinicians ([name] and [name], both have over 10 years of experience in ME/CFS) and using the Canadian Consensus Criteria (CCC) 2003 (1). This study will also include groups of fibromyalgia, a frequent co-morbidity of ME/CFS. The American College of Rheumatology (ACR) 2016 fibromyalgia criteria (25) will be used for screening and followed by clinic diagnosis by a rheumatologist ([name]). The chronic fatigue is defined as self-identified ME/CFS but not confirmed by the two clinicians (i.e., present with other conditions or lack core ME/CFS symptoms) or with other disorders (not ME/CFS or fibromyalgia) that fatigue is a significant symptom. These two groups are included to ensure specificity of the identified neuromarker. Patients with ME/CFS have reduced daily activity because of their illness. However, a sedentary lifestyle itself may affect brain structure and function. Therefore, there is a risk of identifying brain structural or functional differences from ME/CFS sequelae, rather than from the illness per se. This study will mitigate against this problem by selecting HCs with sedentary lifestyles. A sedentary lifestyle will be defined as spending <60 min in moderate or high-intensity activity (i.e., exercise) per week (26). Furthermore, activity level will be monitored by the Actigraph GT3X-BT device (ActiGraph LLC., United States) for 14 days. The recorded activity level will be included as covariates for all statistical analyses but will not change participants' eligibility.

The inclusion criteria include adult individuals who express an interest, meet each group definition, and are confirmed by clinicians.

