The exclusion criteria include individuals (1) out of the age range, (2) pregnant, (3) with severe intellectual or mental impairment preventing them from fully understanding the study to give consent, (4) with mental disorders including post-traumatic stress disorder, obsessive compulsive disorder, schizophrenia, and bipolar disorder, (5) with a known other neurological disorder, (6) who cannot read and communicate in English, (7) recruited by supervising relationship or where a conflict of interest exists, (8) with alcohol or substance related disorder, (9) with BMI >35, (10) smoking (including marijuana or substance usage), (11) with diabetes, hypertension, or uncontrolled hyperlipidaemia, (12) currently on medication acting on the brain, (13) with a clinical diagnosis of hemochromatosis, (14) with a double copy of the Haemochromatosis gene, (15) who experienced migraines more than six times a year before the onset of their symptoms. A researcher will check the exclusion criteria at the screening stage. After the screening process, a differential diagnostic list will be completed by each participant and discussed with two clinicians for diagnosis of ME/CFS during clinical interviews.

Additional exclusion criteria for HCs include individuals (1) with a chronic disease, i.e., a condition that last 1 year or more and require ongoing medical attention or limit activities of daily living or both, including heart disease, stroke, lung cancer, colorectal cancer, depression, type 2 diabetes, arthritis, osteoporosis, asthma, chronic obstructive pulmonary disease, chronic kidney disease, and (2) who experience migraines more than six times a year, and (3) who do more than 60 min in moderate or high-intensity activity per week.

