#### Actigraphy

Participants will be given a GT3X-BT device with a heart rate monitor to wear 7 days before the MRI. The heart rate monitor is to be worn for 24 h. After the MRI scan, participants will be given another GT3X-BT device to wear for 7 days with a 24-h heart rate monitor to be worn on the next morning of the MRI scan. We will collect actigraphy data before and after the MRI scanning (i) to obtain a robust estimations of activity levels, sleep qualities, and heart rate variabilities and (ii) to investigate sleep quality and heart rate variability changes after a moderate exertion (MRI scanning) in ME/CFS.

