### Data analysis plan

The measured variables will firstly be tested for normal distribution. Equivalent non-parametric methods will be used if any variable does not exhibit a normal distribution. The activity measure, body mass index, age, depression, and anxiety will be included as covariates for all statistical analyses. The false discovery rate (FDR) will be used to correct for multiple comparisons.

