#### Actigraphy data

The metabolic equivalent of the task from the GT3X_BT watch will be averaged over 14 days as the activity measure for each participant. The sleep outputs of the GT3X-BT watch, including latency, efficiency, total time in bed, total sleep time, wake after sleep onset, number of awakenings, and averaged awakening time calculated using the Cole-Kripke algorithm (31), will be averaged as objective sleep measurements for each participant. The 24-h heart rate will be downloaded and averaged to generate low- (< 0.1 Hz) and high-frequency (> 0.2 Hz) during awake and sleep for each participant.

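### The activity covariate used in every analysis includes the week after the scan, and a null from the model adjusted for activity and mood would not by itself show that the groups do not differ

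*Protocol article*

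**What the plan says.** The Data analysis plan fixes one covariate set for everything: "The activity measure, body mass index, age, depression, and anxiety will be included as covariates for all statistical analyses". The abstract gives the same list with sex added: "The activity measure, body mass index, sex, age, depression, and anxiety will be included as covariates for all statistical analyses".

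The activity measure is the metabolic equivalent from the wrist device, which "will be averaged over 14 days as the activity measure for each participant" (Actigraphy data). The Actigraphy section shows how the 14 days arise: one device is worn for 7 days before the MRI and another for 7 days after it. Two reasons are given. One is a robust estimate of activity, sleep and heart rate variability. The other is to study sleep quality and heart rate variability "changes after a moderate exertion (MRI scanning) in ME/CFS".

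On the link between illness and covariates, the recruitment section says: "Patients with ME/CFS have reduced daily activity because of their illness". It then gives the reason for controlling activity: "there is a risk of identifying brain structural or functional differences from ME/CFS sequelae, rather than from the illness per se". For the same reason it recruits sedentary healthy controls. The Introduction says that many patients "are often left depressed by the lack of a diagnostic certainty" and of medical understanding. The additional exclusions for healthy controls list depression among chronic diseases ("colorectal cancer, depression, type 2 diabetes, arthritis, osteoporosis"). The mental disorders named in the exclusions for all participants do not include depression.

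**The concern.** There are two related problems.

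The first is timing. A covariate meant to stand for a participant's usual inactivity should be fixed before the outcome is measured. Here half of it is recorded afterwards, in a week that the protocol itself regards as possibly disturbed by the scan, and in ME/CFS in particular. Because the covariate applies to all analyses, it also enters secondary outcome iv, which compares sleep and heart rate variability before and after the scan. There it would adjust for activity in the same week as the response under study.

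The second is interpretation. Aims 1 and 2 are to establish group differences in the hemodynamic response and in dynamic glutamate. The stated model estimates those differences at equal activity, depression and anxiety. If some of a real difference is shared with activity or mood, the fully adjusted result can be null although the groups differ. The article presents the study as a basis for decisive conclusions, so a null result would carry weight.

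**Working it through.** The plan gives no figure for this point, so there is none to reproduce. The check sets the passages side by side and uses simple algebra.

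**1. Window of the activity covariate.** Inputs: 14 days (Actigraphy data), made up of 7 before and 7 after the scan (Actigraphy). Post-scan share = 7/14 = 0.5. With B the mean over the days before and P the mean over the days after, the covariate is A = (7B + 7P)/14 = (B + P)/2. If the scan shifts a group's post-scan mean by δ, then A shifts by 7δ/14 = δ/2.

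**2. Effect on the adjusted comparison.** With the slope b of the outcome on activity held fixed, a shift confined to ME/CFS changes the adjusted difference between ME/CFS and another group by −b × δ/2. The document gives neither b nor δ, so neither the size nor the direction can be stated. With the pre-scan mean B as covariate, this term is zero by construction.

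**3. What the fully adjusted model estimates.** For the same participants in linear models without interactions:

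difference adjusted for age, sex and BMI = fully adjusted difference + b_act·Δ_act + b_dep·Δ_dep + b_anx·Δ_anx

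The b terms are slopes from the full model. The Δ terms are group differences in each covariate after age, sex and BMI. A fully adjusted difference of zero therefore fits two situations: no difference at all, or a difference equal to the sum of the three products. The full model alone cannot tell these apart. The two models side by side can.

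**4. What the protocol says about each covariate.**

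| Covariate | Described as a consequence of illness? | Effect of the design on the group gap | Reason given for adjusting |
|---|---|---|---|
| Activity | Yes, directly | Narrowed: healthy controls must do less than 60 min of moderate or high-intensity activity per week | Yes: to separate sequelae from the illness itself |
| Depression | Indirectly: tied to lack of diagnosis and of medical understanding | Widened: depression excluded as a chronic disease in healthy controls only | None specific |
| Anxiety | No | Nothing stated | None specific |

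The reason given for activity concerns inactivity that comes with the illness. It does not extend to the week after the scan.

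**5. Size.** A figure for lost power or removed effect would need the group gaps on the covariates, their correlations and their slopes on the outcomes. None is given. The power analysis (Figure 4) names the covariates and says nothing of how they relate to group.

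**The case against.** The strongest reply is that adjusting for activity is the declared purpose. The recruitment section wants differences due to the illness rather than to inactivity, so removing the activity-related part is intended, and a total effect is a different question. This stands, and the planned model should be kept. Selecting sedentary healthy controls also narrows the activity gap.

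On the 14 days, the protocol gives a reason (a more robust estimate), and the after-effects it names are in sleep and heart rate variability rather than activity. Both points are fair and limit how serious the timing problem is. They do not make the post-scan week a measure of pre-existing inactivity, and they do not help the before/after comparisons.

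On depression, the general exclusions bar people currently on medication acting on the brain, which may limit depression in the patient groups. Depression and anxiety are also plausible confounders of task imaging. A condensed article need not argue for each covariate, and a reduced-covariate model may be in an analysis plan that is not shown. For that reason the second model is offered as an improvement and not reported as an omission.

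A reader might infer that the protocol calls all three covariates consequences of the illness. It does not: anxiety is never described so, and the remark on depression concerns lack of diagnosis and understanding. A reader might also infer that the design separates the groups on activity. For activity it does the reverse.

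**Conclusion.** The point holds in a limited form. The timing problem follows directly from the text: half of the activity covariate is measured after the imaging outcomes and after a scan treated as an exertion, and the stated reason for controlling activity does not cover that week. The interpretive problem also holds: the planned ANCOVA estimates a difference net of activity and mood, and a null from it alone does not show that the groups do not differ.

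A reader might go further and conclude that real differences will be adjusted away, or attach a figure to lost power. The document does not support either. Both depend on covariate gaps, correlations and slopes that it does not give, and a single inflation factor for one pair of groups would not carry over to a four-group test. The conclusion rests only on the stated measurement window, the stated covariate list and the protocol's own remarks on activity and depression. It is a cheap improvement and does not call for replacing the primary model.

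**What to change.** 1. Build the activity covariate from the 7 pre-MRI days only, for all analyses. The cost is a slightly noisier mean than one over 14 days. The post-scan week stays available for the before/after-scan outcomes.
2. Keep the planned fully adjusted ANCOVA, and say that it targets a difference net of activity, depression and anxiety.
3. Report beside it the same ANCOVA with age, sex and BMI only. List sex explicitly: the abstract and the Discussion include it, but the list in the Data analysis plan does not. The cost is one extra model per outcome on data already collected.
4. State that no group difference will be concluded from the fully adjusted model alone. If the two models disagree, report the difference as shared with activity or mood, not as absent.

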#### Actigraphy data

The metabolic equivalent of the task from the GT3X_BT watch will be averaged over 14 days as the activity measure for each participant. The sleep outputs of the GT3X-BT watch, including latency, efficiency, total time in bed, total sleep time, wake after sleep onset, number of awakenings, and averaged awakening time calculated using the Cole-Kripke algorithm (31), will be averaged as objective sleep measurements for each participant. The 24-h heart rate will be downloaded and averaged to generate low- (< 0.1 Hz) and high-frequency (> 0.2 Hz) during awake and sleep for each participant.

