### The secondary outcomes

i To compare brain structural and functional differences and associations with symptoms among ME/CFS, fibromyalgia, chronic fatigue, and healthy controls (HCs).ii To establish *group* differences in high-frequency heart rate variability and associated fMRI signal changes in ME/CFS.iii To establish *group* objective sleep quality differences and associated brain structure and function differences in ME/CFS.iv To establish *group* differences in sleep measures and changes low- and high-frequency heart rate variability during awake and sleep before and after MRI scanning.v To establish the repeatability of fMRS measures.

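### The 14-day mean MET, read plainly, includes the hours in bed, so adjusting total time in bed and total sleep time for it biases their group comparisons whenever waking activity differs

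*Protocol article*

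**What the plan says.** All references are to the protocol article.

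- **Covariate.** Actigraphy data: "The metabolic equivalent of the task from the GT3X_BT watch will be averaged over 14 days as the activity measure for each participant". Nothing restricts this mean to waking hours.
- **Scope.** Data analysis plan: "The activity measure, body mass index, age, depression, and anxiety will be included as covariates for all statistical analyses". The section on recruitment and selection repeats it: "The recorded activity level will be included as covariates for all statistical analyses but will not change participants' eligibility". Sleep outcomes are not exempted.
- **Sleep measures.** Actigraphy data takes them from the same type of watch: "The sleep outputs of the GT3X-BT watch, including latency, efficiency, total time in bed, total sleep time, wake after sleep onset, number of awakenings", together with average awakening time. These "will be averaged as objective sleep measurements for each participant".
- **Recording.** Actigraphy: "Participants will be given a GT3X-BT device with a heart rate monitor to wear 7 days before the MRI", and a second device is worn for 7 days after the scan. One 7 + 7 day collection therefore serves both activity and sleep.
- **Use.** Secondary outcome iii concerns group "objective sleep quality differences and associated brain structure and function differences in ME/CFS". Secondary outcome iv concerns group "differences in sleep measures and changes low- and high-frequency heart rate variability during awake and sleep before and after MRI scanning".
- **Expected imbalance.** The recruitment section says that daily activity is reduced in ME/CFS because of the illness. It also says that healthy controls are chosen to be sedentary.

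**The concern.** A watch that scores sleep is worn at night, so a MET mean over the whole 14 days mixes hours at rest in bed with hours up and about. A participant who spends longer in bed has a lower mean even if waking activity is unchanged. Total time in bed and total sleep time would then be regressed on a quantity that they partly determine.

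This differs from asking whether activity is a confounder or a consequence of illness. The induced slope appears even when waking activity and sleep are unrelated. It reaches the group contrast as soon as the groups differ in waking activity, and the article expects that they will. With no true difference, patients would tend to appear to spend less time in bed or asleep. A truly longer time would be understated.

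**Working it through.** The article gives no figure for the sleep analyses, so there is none to reproduce.

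**Inputs from the article.** 91 ME/CFS and 91 healthy controls; 87% valid data (Power analysis figure), so 91 × 0.87 = 79 per group; two-sided test at 0.05.

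**Assumed inputs, not in the documents.** Hours in bed S: mean 8, SD 1. MET in bed: 1.0. Control waking MET W: 1.3 to 1.5, SD 0.10 to 0.30. Patients' waking MET lower by d = 0.05 to 0.20. S and W independent within each group. Two groups, and no covariate other than activity.

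**Step 1: the covariate.** M = [S × 1.0 + (24 − S) × W] / 24. One more hour in bed changes M by −(W − 1)/24; at W = 1.4 this is −0.4/24 = −0.017.

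**Step 2: the induced slope.** Let w be a group's mean waking MET. Within groups:
- Cov(S, M) = −[average of (w − 1)]/24 × Var(S)
- Var(M) ≈ average of [(w − 1)/24]² × Var(S) + (16/24)² × Var(W) + Var(S) × Var(W)/576
- slope b = Cov(S, M)/Var(M)

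**Step 3: the adjusted difference.** It equals ΔS − b × ΔM. With no true difference, ΔS = 0 and ΔM = −(16/24) × d.

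*Largest case* (1.5 v 1.3, SD 0.10, a gap of 2 SD): Cov = −0.4/24 = −0.01667. Var(M) = 0.000295 + 0.004444 + 0.000017 = 0.004757. b = −3.50 and ΔM = −0.133. Adjusted difference = −(3.50 × 0.133) = −0.47 h, or 28 minutes.

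*Middle case* (1.4 v 1.3, SD 0.15): Cov = −0.35/24 = −0.01458. Var(M) = 0.000217 + 0.010000 + 0.000039 = 0.010256. b = −1.42 and ΔM = −0.067. Adjusted difference = −0.095 h, or 6 minutes.

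*Mild case* (1.3 v 1.1, SD 0.30): Cov = −0.2/24 = −0.00833. Var(M) = 0.040243. b = −0.207 and ΔM = −0.133. Adjusted difference = −0.028 h, or 2 minutes. With SD 0.30 and a gap of only 0.05 it is under 1 minute.

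**Step 4: simulation** (79 v 79; model S on group and M; 4,000 runs with no true difference, 2,000 with a true +1.0 h):

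| Control waking MET | SD | Gap | Adjusted difference, none true (h) | Rejection | True +1.0 h estimated as |
|---|---|---|---|---|---|
| 1.5 | 0.10 | 0.20 | −0.47 | 58% | 0.46 |
| 1.4 | 0.10 | 0.10 | −0.20 | 20% | 0.74 |
| 1.4 | 0.15 | 0.10 | −0.10 | 9% | 0.88 |
| 1.4 | 0.15 | 0.05 | −0.05 | 6% | 0.92 |
| 1.3 | 0.30 | 0.20 | −0.03 | 5% | 0.97 |
| 1.4 | 0.15 | 0 | 0.00 | 6% | 0.97 |

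The simulated differences agree with the formula. With waking MET as the covariate, the same runs give about 0.0 h and 1.0 h, with rejection near 5% throughout.

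**Step 5: change from before to after MRI.** In the largest case, with an assumed week-to-week SD of 0.5 h, adjusting the change in time in bed for the 14-day mean gives 0.00 h and 5% rejection. The mean weights both weeks equally, so the shared part cancels.

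**The case against.** The strongest objection is that the article never says night hours enter the MET mean. Wear-time and epoch rules are details that an article may leave to a full protocol, and if that document uses waking MET the problem disappears. This stands as a limit: inclusion of the hours in bed is the plain reading, not a stated fact. It does not remove the point. The article fixes the device, the metric, the averaging window and the scope, and those rules, followed as written, produce the bias.

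The size is also uncertain. Every MET value is assumed, and controls are selected as sedentary, which should narrow the gap. That stands too. However, the selection is on moderate or high-intensity activity, not on total activity, and the plan still expects to need adjustment.

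A reader might infer that all the sleep results are compromised. The documents do not support that. Of the seven measures listed, only total time in bed and total sleep time are direct components of a 24-hour mean. Latency, efficiency, wake after sleep onset, number of awakenings and average awakening time share the movement record, but no bias was shown for them, and several are the natural measures of sleep quality under outcome iii. Under outcome iv only comparisons of levels are exposed.

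**Conclusion.** The point holds for group comparisons of the level of total time in bed and total sleep time under secondary outcomes iii and iv. As written, these are adjusted for a covariate that, on the plain reading, falls as they rise. With lower waking activity in ME/CFS, the bias is towards less time in bed or asleep.

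Across the assumed values, the spurious difference is from 2 minutes or less to just under 30 minutes, with 5% to about 60% rejection at a nominal 5%. It would be wrong to read the upper end as the expected error rate, because it needs an activity gap of 2 SD. With equal activity there is no spurious difference, although a true +1.0 h is still slightly understated (0.97 h in the middle setting). Changes from before to after MRI are unaffected. So are the primary outcomes (HRF, glutamate, neuromarker), which contain no sleep measure. The matter is worth correcting because the direction is predictable and the remedy is cheap.

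**What to change.** In Actigraphy data, state that for the total time in bed and total sleep time comparisons the activity covariate is MET averaged over waking hours only, leaving out periods that the same recording scores as time in bed. Applying this to all sleep outcomes is simplest. Alternatively, leave activity out of those models and say so as an exception to the rule that it enters all analyses; the group difference is then not adjusted for activity. If a waking-hours mean was always intended, one clause saying so settles the matter.

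The cost is a sentence and a re-computation from recordings already collected. Adjusting for waking MET costs some power when the groups differ in activity, as any activity adjustment does. With control waking MET 1.4, SD 0.15, a gap of 0.15 and a true difference of 0.5 h, power was 79%, against 87% unadjusted and 50% with the 24-hour mean.

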I Structural MRI (sMRI) using a T1-weighted magnetization prepared rapid gradient-echo sequence (MPRAGE): 208 slices, dimension 256 × 256, voxel size 1 mm × 1 mm × 1 mm, TR/TE 2,200/1.71 ms, flip angle 7°.II A set of resting-state fMRI (rsfMRI, 192 volumes) using a multiband EPI sequence: 108 slices, dimension 126 × 126, multiband = 4, dimension 138 × 138, 1.6 mm^3^ isotropic voxel, TR/TE 2,500/42 ms, flip angle 75°. Participant will be instructed to keep their eyes open with fixation of a cross for 8 min acquisition. Heart rate will be recorded simultaneously using pulse oximetry from the MRI scanner.III A set of task fMRI (tfMRI, 800 volumes) using a multiband EPI sequence (60 slices, multiband = 8, dimension 74 × 74, 3 mm^3^ isotropic voxels, TR/TE 800/33 ms, flip angle 65°) while participants perform a symbol digit modalities test (SDMT), which is widely used for cognitive evaluation of information processing speed. A semi-random design, which simultaneously achieves maximum estimation efficiency and detection power, (30) was used (Figure 2). The paradigm is incorporated into the scanner's fMRI sequence for general linear modeling of BOLD signal changes associated with tasks. Brain regions with BOLD signal changes associated tasks are used for voxel location of functional magnetic resonance spectroscopy (fMRS).IV A set of breath-holding fMRI (BH fMRI, 324 volumes) will be acquired using the same pulse sequence and parameters as tfMRI above. Participants perform 6 BH tasks; each BH task consists of 14.4 s (18 fMRI volumes) natural breath, 3 paced breathing (4.8 s each with 2.4 s breath in and out, respectively) of 14.4 s and a 14.4 s end-expiration breath-hold.V A set of fMRS using the HERMES (Hadamard Encoding and Reconstruction of MEGA-Edited Spectroscopy) acquisition method with TR/TE = 2,000/23 ms. The task paradigm is the same as the tfMRI paradigm (Figure 2), during which 16 and 5 measurements (averaged from 8 volumes per measurement) are collected for task and resting block, respectively. A single cuboid voxel, 20 mm (superior-inferior), 27 mm (anterior-posterior), and 12 mm (left-right), covering the left dorsal prefrontal cortex, is adjusted according to individual BOLD activation maps (Figure 3).VI A set of diffusion tensor images (DTI) using a multiband EPI sequence (72 slices, multiband factor 3, dimension = 114 × 114, voxel size 2 × 2 × 2 mm^3^, TR/TE = 4,500/123 ms; free diffusion mode, 96 diffusion directions, bipolar diffusion scheme with two diffusion weighting of b = 0 and b = 2,500, phase encoding direction = anterior to posterior). Six volumes of b = 0 with phase encoding direction in posterior to anterior are also collected for the eddy current correction.VII A final set of rsfMRI will be collected using the same setting as II.

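### The bands fixed for 24-hour heart rate variability leave 0.1–0.2 Hz uncounted and give the low band no lower limit, so breathing rate and slow drift may confound secondary outcome iv

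*Protocol article*

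**What the plan says.** The heart rate variability measures are defined in one sentence of the protocol article (Data analysis plan, Actigraphy data). It begins "The 24-h heart rate will be downloaded and averaged" and gives the bands as "averaged to generate low- (< 0.1 Hz) and high-frequency (> 0.2 Hz) during awake and sleep". As written, the low band has an upper limit only, the high band has a lower limit only, and the range between 0.1 and 0.2 Hz is assigned to neither.

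On the recording, the Actigraphy section under Data collections says "The heart rate monitor is to be worn for 24 h". One such recording is made before the MRI and another after it.

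Two secondary outcomes use heart rate variability. Outcome iv concerns "low- and high-frequency heart rate variability during awake and sleep before and after MRI scanning". Outcome ii concerns group "differences in high-frequency heart rate variability and associated fMRI signal changes in ME/CFS".

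On adjustment, the Data analysis plan says "The activity measure, body mass index, age, depression, and anxiety will be included as covariates for all statistical analyses". The activity measure is the metabolic equivalent, which "will be averaged over 14 days as the activity measure for each participant". No respiratory covariate is listed, and no respiratory recording is described for the 24-hour monitoring.

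**The concern.** High-frequency heart rate variability is read as the fluctuation of heart rate at the breathing frequency. This is general physiology and is not stated in the article. If a person breathes at 6 to 12 per minute, that fluctuation lies between 0.1 and 0.2 Hz, where the plan counts nothing. Such a person scores low in the high band whatever the vagal activity. Power can also cross the 0.2 Hz edge between waking and sleep because breathing rate changes, which is a problem for an outcome that compares those two states.

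The low band has the opposite fault. Without a lower limit, a record lasting hours lets in very slow changes in heart rate from posture, movement and time of day. These differ between waking and sleep for reasons other than autonomic regulation. They may also differ before and after the scan, which the Actigraphy section treats as a moderate exertion for people with ME/CFS.

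A difference in breathing or movement could then be taken for an autonomic difference, or a true difference among slow breathers could be missed. The article has committed itself to numeric edges, so this is a rule that yields a poorer measure if followed, and not just detail left to a fuller document.

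**Working it through.** The plan states no sample size, power or expected value for these outcomes, so there is no figure of its own to reproduce. The check has three parts.

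**1. The gap in breaths per minute**

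Breaths per minute = 60 × Hz.

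- 0.1 × 60 = 6 per minute (period 10 s)
- 0.2 × 60 = 12 per minute (period 5 s)

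**2. How many people breathe below the high band**

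The article gives no spontaneous breathing rates. Assume that participants' average rates are normal with mean m and SD s. The share below 12 per minute is Φ((12 − m)/s).

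| Assumed mean | SD 2 | SD 3 |
|---|---|---|
| 13 | Φ(−0.50) = 31% | Φ(−0.33) = 37% |
| 14 | Φ(−1.00) = 16% | Φ(−0.67) = 25% |
| 16 | Φ(−2.00) = 2% | Φ(−1.33) = 9% |
| 18 | Φ(−3.00) = about 0% | Φ(−2.00) = 2% |

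The loss is material around 14 per minute or less and small at 16 or more. Because outcome iv compares waking with sleep, what matters is the rate in each state, and a person can lie above the edge in one and below it in the other.

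**3. What an unbounded low band can contain**

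The article gives no spectrum. Assume power proportional to 1/f^b below 0.1 Hz, with the lowest frequency equal to 1/T for a record of length T. The share at periods longer than 5 minutes (300 s) is:

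- b = 1: ln(T/300) / ln(T/10)
- b = 1.2: (T^0.2 − 300^0.2) / (T^0.2 − 10^0.2)

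| Record analysed whole | b = 1 | b = 1.2 |
|---|---|---|
| 8 h asleep (T = 28,800 s) | ln 96 / ln 2,880 = 57% | (7.80 − 3.13)/(7.80 − 1.58) = 75% |
| 16 h awake (T = 57,600 s) | ln 192 / ln 5,760 = 61% | (8.96 − 3.13)/(8.96 − 1.58) = 79% |
| 5-minute windows (T = 300 s) | 0% | 0% |

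The 8 and 16 hours are also assumed. The size of this effect depends on the window: most of the low-band power under whole-record analysis, none at these periods with 5-minute windows. The gap in part 2 is the same whatever the window.

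**Whether the covariates can correct it**

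The activity covariate is one number per participant, pooled over the 7 days before and the 7 days after the scan. It takes the same value awake and asleep, and before and after MRI. It can adjust group comparisons for average activity, but it cannot represent a change in movement within a person, which is what outcome iv contrasts. Breathing rate is not among the covariates.

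**The case against.** The strongest reply is that none of this shows a bias in the trial. The documents contain no breathing rates, no heart rate spectra and no group difference in respiration. A loss of respiratory power that is similar in all groups costs sensitivity but creates no false difference. This stands. A reader might infer that the outcomes will track breathing and daily activity instead of autonomic function; the documents do not support that. They support only that the measures may be confounded.

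Window length, detrending and the beat-to-beat source commonly sit in a fuller plan. This also stands, and short windows would largely remove the low-band problem. They would not close the gap, because the article itself fixes the edges.

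On activity, the article selects sedentary controls and adjusts for recorded activity (The recruitment and selection of the sample population). That mitigates in part, mainly for comparisons between groups, and not for the contrasts within a person.

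Three further inferences should be resisted:

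- **Averaging.** The sentence can be read as averaging the heart rate signal before taking the bands, which would smooth away fast variation. The two preceding sentences use the same verb for summarising to one value per participant, so the wording is ambiguous and no more can be claimed.
- **Paced breathing.** The breath-hold task (Multimodal MRI, item IV) uses "3 paced breathing (4.8 s each with 2.4 s breath in and out, respectively". That is 60/4.8 = 12.5 per minute, or 0.208 Hz, close to the edge. But it is a scanner task unconnected with the 24-hour recording, and it lies inside the high band. It is no evidence here.
- **Outcome ii.** Heart rate is also recorded by pulse oximetry during resting-state fMRI (Multimodal MRI, item II), a plausible source for that outcome. It is affected only if the same bands are applied.

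**Conclusion.** The point holds as a defect in a stated measurement rule. The bands leave 6 to 12 breaths per minute uncounted and set no floor for the low band. High-frequency variability may be understated for 16% to 25% of participants if breathing averages 14 per minute, and for 2% to 9% if it averages 16, with SD 2 to 3 in both cases. All of these breathing figures are assumptions. The low band may be dominated by slow drift if long records are analysed whole, and much less so with short windows or detrending, which the article does not mention.

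The direction and size of any resulting bias cannot be shown from the documents. Secondary outcome iv is exposed in its awake/sleep and before/after contrasts, and outcome ii conditionally. The primary aims are unaffected. The change is worth making because it is cheap and improves the measure.

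**What to change.** In the Actigraphy data section:

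1. State both limits of each band and make the bands adjoin. One example is low 0.04–0.15 Hz and high 0.15–0.40 Hz; the high band then covers 0.15 × 60 = 9 to 0.40 × 60 = 24 breaths per minute. These limits are illustrative and do not come from the documents.
2. State that band power is computed from beat-to-beat intervals in short windows, for example 5 minutes.
3. State that window band power, and not heart rate, is averaged over the awake and sleep periods.
4. Say whether outcome ii uses the same bands and which recording it comes from.

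Under the same assumptions, the share below the high band's lower edge falls to Φ((9 − 14)/2) = 1% to Φ((9 − 14)/3) = 5% at a mean of 14 per minute, and to at most Φ((9 − 16)/3) = 1% at a mean of 16.

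The cost is a few sentences and reprocessing of existing recordings, with no new data, provided that beat-to-beat data were stored. That should be confirmed now: Progress and plan reports 110 of the planned 288 participants recruited by 20 May 2022. Some dependence on breathing rate remains outside 9 to 24 per minute, and it should be acknowledged when the results are interpreted.
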